### Statistical analysis

Continuous variables will be presented as mean ± standard deviation (SD) or as median with interquartile range (IQR), and categorical variables (e.g., gender) will be reported as frequencies and percentages. The Kolmogorov-Smirnov test will be used to test for normal distribution. Accordingly, the Student t-test or Mann-Whitney U test will be used to test for statistically significant differences. The Chi-Square or Fisher Exact test will be used for statistical distribution analysis of categorical variables. Kaplan-Meier analyses will be performed for survival and safety outcomes. Linearized rates and actuarial probability statistics will be used where appropriate for adverse event reporting. A *P*-value of < 0.05 will be considered statistically significant. Statistical analysis will be performed using SPSS Version 24.0 (Armonk, NY, IBM Corp.).

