## Methods/design

The INDURE registry is a prospective, open-label, multicentre, international registry with a follow-up of 5 years to assess the clinical outcomes of patients younger than 60 years of age who undergo surgical AVR with the INSPIRIS RESILIA aortic valve (Edwards Lifesciences). The registry is conducted according to ISO 14155:2011. Approximately 400 patients will be enrolled across 20–22 European sites (including Austria, Belgium, France, Germany, Italy, the Netherlands, Spain, and UK) and Canada, resulting in about 20 patients per site. It was estimated, from the COMMENCE Trial dataset [17, 20], that freedom from time-related valve safety events at 1-year (composite endpoint according to VARC-2 criteria) is around 91.5%, suggesting that 400 patients will arrive at a 95% confidence interval (CI) of ±2.14%. Lower rates (80%) will broaden the 95% CI to ±3.92% and higher rates (99%) narrow it down to ±1%.

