### Objectives

The primary objectives (Table 1) are to 1) determine the time-related valve safety at 1-year (composite endpoint according to the VARC-2 criteria) depicted as freedom from events [23] and 2) determine freedom from stage 3 SVD following the Salaun definition at 5 years [23, 24]. Events include SVD (either valve-related dysfunction, defined by haemodynamic parameters or the need for repeat procedure), prosthetic valve endocarditis, prosthetic valve thrombosis, thromboembolic events (e.g., stroke) and valve-related bleeding.

**Table 1 Tab1:** Registry objectives

**Primary objectives**	Time-related valve safety at 1 year (composite endpoint according to VARC-2 [23] depicted as freedom from the following events: • SVD (valve-related dysfunction [MPG ≥20 mmHg, EOA ≤0.9–1.1 cm^2^ and/or DVI < 0.35 m/s, AND/OR moderate or severe prosthetic valve regurgitation], requiring repeat procedure [TAVI or SAVR]) • Valve-related dysfunction • Requirement of repeat procedures (Re-intervention) • Prosthetic valve endocarditis • Prosthetic valve thrombosis • Thromboembolic events (e.g., stroke) • Valve-related VARC bleeding
	To determine freedom from stage 3 SVD following [24] at 5 years
**Secondary objectives**	Haemodynamics and durability: • Haemodynamic performance of the INSPIRIS RESILIA Aortic Valve™ including PPM • SVD following Salaun [24] • Description of potential ViV procedures and clinical outcome including follow-up
	Clinical outcomes: • NYHA functional class compared to baseline • Freedom from valve-related rehospitalisation
	Quality-of-life: • 3–6-month, 1-year and 3-year change from baseline in quality-of-life assessed by the KCCQ and SF-12 Health Survey
**Exploratory: Rehospitalisation and costs**	Length of hospital stay
	Length of time in intensive care unit
	Time to return to work
	Rate of valve-related rehospitalisation and associated costs (average costs per country)
	Rate of transfusion for bleeding and associated costs (average costs per country)
	Costs of a major bleeding event
	Costs of daily anticoagulation
	Rate of re-intervention for valve degeneration and associated costs (average costs per country)
**Exploratory: Safety**	SVD
	Non-SVD
	Thromboembolic events (e.g., stroke)
	Valve thrombosis
	All bleeding/haemorrhage
	Major bleeding/haemorrhage
	All paravalvular leak
	Major paravalvular leak
	Endocarditis
	All-cause mortality
	Cardiac-related mortality
	Valve-related mortality
	Valve-related re-intervention
	Conduction disturbances

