### Appreciation of the study design

The INDURE registry is a prospective, open-label, multicentre, international registry. The multinational nature of this registry increases the applicability of findings to clinical practice all over Europe and Canada. However, it has no control group making a comparison of different bioprosthetic valves or valve generations impossible. Furthermore, there is no comparison of the bioprosthetic valve data with the outcomes of mechanical valve implantation, which would be desirable, but goes beyond the possibilities of such a project. Because of the multicentre design, an Echo CoreLab has been established to have a uniform assessment of SVD over the time course of the 5-year follow-up. We considered establishing an MSCT CoreLab, as has been incorporated in the RESILIENCE trial, but it would have violated the non-interventional nature of the INDURE registry as most sites reported that an MSCT is not standard-of-care at their institution, which may be considered as a limitation. Nonetheless these data can be documented in case they are available from routine practice. Finally, the same INSPIRIS RESILIA valve will be used in all patients in the INDURE registry which will abolish any bias introduced by the use of different bioprosthetic valves.

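### A Kolmogorov-Smirnov pre-test lets the data, and mainly the sample size, decide whether continuous secondary and exploratory outcomes are tested on means or on ranks

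*Protocol article*

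**What the plan says.** All of the rule stands in the protocol article, section Statistical analysis. Continuous variables are to be shown either as mean with SD or as median with interquartile range, with no variable assigned to either form. Then: "The Kolmogorov-Smirnov test will be used to test for normal distribution". The following sentence makes that result decisive: "Accordingly, the Student t-test or Mann-Whitney U test will be used to test for statistically significant differences". A P-value below 0.05 "will be considered statistically significant". The section does not say whether the pre-test is applied to pooled data or per group, at what level, or whether it is corrected for estimating the mean and SD from the same data.

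The continuous outcomes in Table 1 (section Objectives) include haemodynamic performance, "change from baseline in quality-of-life assessed by the KCCQ and SF-12 Health Survey", "Length of hospital stay", time in intensive care, and several cost items given as country averages. On size, "Approximately 400 patients will be enrolled", "resulting in about 20 patients per site" (section Methods/design). The section Appreciation of the study design adds that "it has no control group", so any comparison is between subgroups or over time. Survival and safety outcomes go to Kaplan-Meier analysis.

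**The concern.** A normality test answers whether a departure from normality is detectable, which depends on n. Whether the mean is the right quantity, and whether the t-method is accurate for it, are different questions, and the second runs the other way: the t-method becomes more accurate as n grows, just when the pre-test becomes more likely to reject.

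The two tests also answer different questions. Student's t compares means. Mann-Whitney compares the probability that a value from one group exceeds a value from the other. Under this rule one quality-of-life score could be judged on means and another on ranks, or the same variable on means in a subset and on ranks in the whole cohort, with the choice known only after the data are seen. For a change from baseline or an average cost, the mean is the natural quantity, and a rank P-value beside it would not be a test of it.

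**Working it through.** **Inputs from the protocol article.** About 400 patients; about 20 per site, taken as an example of a small subset; significance at P<0.05, taken as two-sided. The article gives no SD, skewness or subgroup size and no figure for this rule that could be reproduced. **Assumptions.** Log-normal shapes with log-SD s from 0.5 to 1.0 (mean/median ratio exp(s²/2): 1.13 at 0.5, 1.50 at 0.9, 1.65 at 1.0) and the group sizes shown. Simulations used 10,000 samples per one-sample setting and 5,000 per two-group setting.

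**1. Why sample size drives the pre-test.** The statistic is D = max |Fₙ(x) − Φ((x − mean)/SD)|. Its uncorrected 5% critical value falls roughly as 1.36/√n: 0.294 at n=20 (exact), 0.134 at n=100, 0.067 at n=400. The distance between the log-normal curve and its matching normal curve is fixed by shape: 0.099 at s=0.5, 0.138 at s=0.7, 0.196 at s=0.9. All three lie below the n=20 threshold and above the n=400 threshold. The variable is the same; only n has changed.

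**2. At n=400.**

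| s | Uncorrected rejects | Corrected (Lilliefors) rejects | 95% t-interval covers |
|---|---|---|---|
| 0.5 | 99.98% | 100% | 95.1% |
| 0.7 | 100% | 100% | 95.0% |
| 0.9 | 100% | 100% | 94.2% |

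For milder skewness the result depends on the form used. For gamma data at n=400, samples pass the uncorrected test in about 92% of cases at skewness 0.5 and about 13% at skewness 1; with the correction, about 30% and 0%. Under exact normality the uncorrected form rejects almost never (0 to 0.02% at n=20 to 400) instead of 5%; the corrected form rejects about 5%.

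**3. At n=20, one sample or paired change.**

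| s | Uncorrected rejects | Corrected rejects | t-interval covers, all samples |
|---|---|---|---|
| 0.5 | 1.2% | 35% | 93.1% |
| 0.7 | 5.3% | 55% | 91.2% |
| 0.9 | 14.5% | 72% | 88.7% |
| 1.0 | 19.6% | 80% | 86.5% |

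Passing the pre-test does not pick out the safe samples. Among those that pass the uncorrected form, coverage is 93.0%, 90.8%, 87.0% and 83.9% in the same order.

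**4. Two small groups of equal shape.** At s=0.7, Student's t rejects 4.6% at 20/20 and 4.1% at 10/10; the two-stage rule rejects 4.3 to 5.3%. Skewness largely cancels between groups, so the loss in step 3 does not carry over.

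**5. Large groups, identical distributions.** At 300/100 with s=0.4 in both groups, or 0.6 in both, the two-stage rule rejects 5.0 to 5.2%.

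**6. Large groups, equal means, unequal spread.** Take 300 patients with s=0.4 and 100 with s=0.6, both with mean 1. The log-means are −0.08 and −0.18. The quantity Mann-Whitney tests is Φ((−0.18 + 0.08)/√(0.16 + 0.36)) = Φ(−0.139) = 0.445, not 0.5. Its null standard error is √(401/(12 × 300 × 100)) = 0.0334, so z = (0.5 − 0.445)/0.0334 = 1.65, and the rejection probability is about P(Z > 1.96 − 1.65) = 38%. Simulation: Mann-Whitney alone 39.0%, two-stage rule 38.3% (per group) or 38.8% (pooled), Student's t 11.8%, unequal-variance (Welch) t 6.0%. At 200/200 the rule rejects about 48% and both t-tests about 5%.

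**The case against.** Four objections carry weight.

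**Error rates.** A reader might infer that the rule breaks the 5% level in general. It does not. With identical distributions it stays near 5% (steps 4 and 5), and under-coverage in small samples is a one-sample or paired result, not one for the two-group Student test that the article names.

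**The 39%.** A reader might blame this on the pre-test. Mann-Whitney gives the same figure with no pre-test. The distributions do differ there, so the rejection is wrong only if read as a difference in means. What the pre-test contributes is to route skewed variables to that test. Part of the contrast with 6% also comes from replacing Student's t (11.8%) by Welch's.

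**Reach.** A reader might infer that every bounded or skewed variable is rejected at 400 patients, or that means vanish from the report. Mild skewness often passes, and the article allows means and lists costs as averages. There is no control arm and no named subgroup comparison, and the freedom-from-event primary objectives are not handled by this rule.

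**Condensed article.** A separate analysis plan may assign methods per variable, and its absence here is no fault. But the article does not stay silent: it states a data-driven selection rule, and that rule can be judged as written.

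These objections limit the size of the point. None gives a reason to keep the pre-test.

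**Conclusion.** The point holds with a limited scope. The stated rule makes the tested quantity depend on the data and mainly on n. At the registry's full size it discards a mean analysis that works (coverage 94 to 95%) for clearly skewed variables, and puts in its place a rank hypothesis that does not address a mean change in KCCQ or SF-12 or an average cost. In small samples it offers little protection for one-sample or paired-change intervals, where coverage is about 86 to 93%.

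It affects how continuous secondary and exploratory outcomes are read. The documents do not support a claim that the Kaplan-Meier safety and survival results are compromised or that type I error is generally inflated. All shapes, spread ratios and group sizes are assumptions; the qualitative result follows from a critical value that shrinks with n while the distance from normality does not. Whether the change-from-baseline tests are meant to be paired is a separate question.

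**What to change.** Replace the two sentences on the pre-test and the choice of test with a statement that fixes the analysis per variable in advance:

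- KCCQ, SF-12, haemodynamic measures and costs: mean, or mean change, with a t-based 95% CI; the unequal-variance t-test for any group comparison.
- Length of stay and intensive care time: mean or median, either being defensible, but chosen beforehand.
- Median and interquartile range beside the mean throughout, as description.
- The rank test only as a named sensitivity analysis.

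One caution: the unequal-variance t-test is not exact for a very small, strongly skewed subgroup. At 20 versus 380 with identical log-normal data (log-SD 1.0) it rejected 11.5%, although with the SD doubled in the small group it did better than Student's t (12.7% against 25.8%). A bootstrap interval could be named for such subsets.

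The cost is two sentences and no new data. A few results will appear as means with intervals instead of medians.

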## Discussion

The INDURE registry has been designed to provide prospectively collected data that can be used to elucidate the benefits and risks of the surgical implantation of INSPIRIS RESILIA in patients with AVR who are younger than 60 years of age, as well as the long-term haemodynamic and structural performance of the valve in patients in this age group. Analysis of the data may also provide additional support for the earlier use (e.g., at a younger age) of bioprosthetic valves in patients undergoing AVR.

### Bioprosthetic vs. mechanical valves

Mechanical valves are generally preferred over bioprosthetic valves for younger patients undergoing AVR because of their perceived greater durability with the 15-year rates of redo-surgery being 6.9% for mechanical and 12.1% for biological heart valves [10]. It is suggested that mechanical valves will last throughout the remainder of the patient’s lifetime [25]. Mechanical valves do, however, require daily treatment with anticoagulants, which will increase the risk of bleeding. Lifelong anticoagulation can be difficult for patients with a history of bleeding issues or an increased risk of injury related to an active lifestyle. There may also be dietary restrictions, including reducing the intake of foods rich in vitamin K when taking vitamin K antagonists [26]. Newer (or non-vitamin K) oral anticoagulants (NOACs) are strictly contraindicated in patients with any mechanical prostheses [15, 27, 28]. Next to all the anticoagulation-related problems, reoperations can be needed even in mechanical valves in case of pannus overgrowth. Bioprosthetic valves do not require long-term daily anticoagulants but are at risk of SVD requiring reoperation [26]. The risk/benefit profile of mechanical versus bioprosthetic valves has led to both American and European guidelines on valvular heart disease recommending the use of mechanical valves in patients younger than 50 years [14, 15] with the European version extending this recommendation to patients up to 60 years (class IIa, level C) and the American guidelines considering both mechanical and bioprosthetic valves in patients between 50 and 70 years of age (class IIa, level B, no RCT data). Despite these recommendations, the use of bioprosthetic valves has significantly increased over the last few decades across all age groups [26]. Currently bioprosthetic valves are being developed that avoid the risk of valve required anticoagulation while reducing the reoperation rates seen with earlier generation bioprosthetic valves.

### Determinants and surrogates of valve failure

The ultimate goal when developing durable bioprosthetic valves, which are particularly required for younger patients, is to ascertain an uncompromised haemodynamic function over the very long term with no structural degeneration that would otherwise lead to a requirement for valve replacement or valve-in-valve (ViV) interventions or death [29, 30]. The data required, however, would take 10, 15 or even 20 years to be collected and assessed and, as such, shorter-term surrogates of valve degeneration have been developed which facilitate shorter valve development cycles. The criteria are plenty, but have been recently reviewed by different author groups including Capodanno et al. [31], Dvir et al. [32] and Salaun et al. [24], partly in an attempt to provide standardised definitions of SVD for bioprosthetic aortic valves. The definition of SVD by Salaun [24] (Table 3) has been adopted in the current project as it incorporates terminology proposed by both Dvir [32] and Capodanno [31] and was compatible with the definition used by Pibarot et al. [34] (see below). We will, however, capture the components of the other definitions as well aiming to explore and compare these as well.

**Table 3 Tab3:** Definition of structural valve deterioration of aortic bioprostheses following Salaun [24]

	Stage 0^a^ No SVD	Stage 1^a^ SVD with no HVD ‘Morphological SVD’^b^	Stage 2^a^ SVD with moderate HVD ‘moderate hemodynamic SVD’^b^	Stage 3^a^ SVD with severe HVD ‘Severe hemodynamic SVD’^b^
Valve leaflet morphology and motion by TTE, TEE or MDCT				
Leaflet morphology				
Valve leaflet thickening: At least one leaflet with thickness ≥ 2 mm	Absent	Present	Present	Present
Valve leaflet fibrocalcific remodelling: Hyper echogenicity (TTE/TEE) or hyper density (MDCT) Detectable leaflet calcification at MDCT	Absent	Present	Present	Present
Leaflet motion				
Reduced mobility	Absent	Absent or mild	Mild to moderate	Moderate to severe
Leaflet tear/avulsion	Absent	Absent	May be present	May be present
Valve haemodynamics by TTE				
Mean transprosthetic gradient				
Absolute increase from baseline^c^	< 10 mmHg	< 10 mmHg	10–19 mmHg	≥20 mmHg
Mean gradient at post-AVR echo^d^	< 20 mmHg	< 20 mmHg	20–39 mmHg	≥40 mmHg
Valve effective orifice area				
Absolute decrease from baseline	< 0.30 cm^2^	< 0.30 cm^2^	0.30–0.59 cm^2^	≥0.60 cm^2^
Doppler velocity index				
Absolute decrease from baseline	< 0.1	< 0.1	0.1–0.2	≥0.2
Transprosthetic valve regurgitation^c^				
Worsening compared with baseline	Absent	None	≥1 Grade	≥2 Grades
Grade of regurgitation	None, trace or mild	None, trace or mild	Moderate	Severe
Clinical status		Subclinical	Often subclinical	Generally clinically expressive
New onset or worsening symptoms		Absent	Often absent	Generally present
New onset or worsening LV dilation/hypertrophy/dysfunction		Absent	Generally absent	Often present
New onset or worsening pulmonary hypertension		Absent	Generally absent	Often present

The classification and criteria presented in this table are based on recommendations and standardised definitions of medical societies or group of experts [31–33]

Stage 0 refers to a normal valve. Stage 1 consists in the presence of morphological abnormalities of valve leaflets but with no evidence of HVD. At echocardiography, the leaflets are thickened (> 2 mm), often irregular and hyperechogenic. MDCT without contrast may be used to detect and quantitate macroscopic valve leaflet calcification by the modified Agatston method or the volumetric method. Stage 2 consists in SVD with moderate HVD defined as: (1) an increase in mean transprosthetic gradient ≥10 mmHg since early post-SAVR or TAVI echocardiography with concomitant decrease in valve EOA and DVI; and/or (2) a new onset or worsening of transprosthetic regurgitation by at least one grade with a final grade of moderate. An increase in transprosthetic velocity and gradients with concomitant increase in valve EOA and DVI is actually related to an increase in flow during follow-up and should not be mistaken for an HVD. Stage 3 consists in SVD with severe HVD characterised by: (1) an increase in mean transprosthetic gradient ≥20 mmHg since SAVR or TAVI with concomitant marked decrease in valve EOA and DVI and/or (2) new onset or worsening of transprosthetic regurgitation by at least two grades with final grade of severe regurgitation

*AVR* Aortic valve replacement, *DVI* Doppler velocity index, *EOA* Effective orifice area, *HVD* Haemodynamic valve deterioration, *LV* Left ventricle, *MDCT* Multidetector CT, *SVD* Structural valve deterioration, *SAVR* Surgical aortic valve replacement, *TAVI* Transcatheter aortic valve implantation, *TEE* Transesophageal echocardiography, *TTE* Transthoracic echocardiography

Classification terminology proposed by: ^a^Dvir et al. [32] and ^b^Capodanno et al. [31]

^c^The most important criteria to define haemodynamic HVD is a significant increase in mean transprosthetic gradient with concomitant decrease in valve EOA and DVI; and/or a new onset or a worsening of transprosthetic valve regurgitation

^d^This criterium is corroborative but should not be used in isolation to define HVD

### INDURE in perspective

The RESILIA tissue has been studied in two trials to date [17, 18] with a total of 812 patients showing that its use results in excellent haemodynamic performance and safety up to 2 years. Both the RESILIENCE trial [34] and the INDURE registry were set up in order to assess the long-term performance and structural integrity of bioprosthetic valves using the RESILIA tissue in younger patients. RESILIA tissue incorporates an anti-calcification process, by permanently blocking the residual aldehyde groups that are known to bind calcium. Calcification is known to occur more commonly on bioprosthetic valves than mechanical valves [35]. It, therefore, has the potential to increase valve longevity and consequently reduce re-intervention rates.

Both INDURE and RESILIENCE (Table 4) are prospective studies, including patients with either the INSPIRIS RESILIA valve (INDURE) or any RESILIA tissue bearing valve (RESILIENCE). While INDURE will follow patients from the time of surgery for 5 years, RESILIENCE pursues retrospective inclusion of patients with the first visit being 5-years after surgical intervention and a prospective follow-up (up to year 11 after the implant). On the one hand, INDURE puts emphasis on a combination of time-related valve safety at 1-year, SVD defined according to Salaun [24] using a CoreLab and clinical outcomes, while on the other hand RESILIENCE focuses on the multi-slice computed tomography (MSCT) and echo-based (both CoreLab) prediction of re-intervention or valve-related death. Projected completion dates are 2025 (INDURE) and 2027 (RESILIENCE), respectively.

**Table 4 Tab4:** INDURE vs. RESILIENCE

	INDURE (NCT03666741)	RESILIENCE (NCT03680040)
Valve used	INSPIRIS valves	RESILIA tissue valves
Design	Prospective	Retrospective inclusion, prospective follow-up
Study Start date	26 April 2019	5 November 2018
Baseline	Implantation	5 years
Follow-up	5 years – projected completion 2025	6 years (from year 5 to year 11) – projected completion 2027
Subjects/centres	400 subjects, 20–25 centres (EU and Canada) under the age of 60 years at the time of their SAVR	220 subjects, up to 15 centres (US and EU) under the age of 65 years at the time of their SAVR
Objective	Assess clinical outcomes	Time to valve failure due to valve degeneration requiring re-intervention & early potential predictors of valve durability
Primary endpoints	Time-related valve safety at 1 year (VARC-2)	Time to BVF due to SVD, defined as requiring re-intervention (redo surgery or ViV), or confirmed valve related death, according to Akin criteria [29]
	Rate of severe SVD (stage 3 following Salaun [24]) at 5 years (Echo CoreLab)	
Secondary endpoints	Haemodynamics and durability (Echo CoreLab) Clinical outcomes (NYHA and freedom from rehospitalisation) Quality-of-life (KCCQ & SF-12)	Early possible predictors of valve failure including leaflet calcification and morphological/haemodynamic valve degeneration: -Valve leaflet calcification via CoreLab evaluated MSCT (no contrast) -Haemodynamic performance (Echo CoreLab)

*BVF* Bioprosthetic valve failure, *EU* European Union, *KCCQ* Kansas City Cardiomyopathy Questionnaire, *MSCT* Multi-slice computed tomography, *NYHA* New York Heart Association, *SF-12* Short Form-12, *SVD* Structural valve degeneration, *US* United States, *VARC* Valve Academic Research Consortium, *ViV* Valve-in-valve

Up and beyond INDURE and RESILIENCE there is a third long-term data collection ongoing (IMPACT; NCT04053088) using the INSPIRIS RESILIA valve. It is being conducted in Germany, Austria, Switzerland and The Netherlands and will follow up to 500 patients for 5 years. The principal objective of IMPACT is the assessment of the impact of comorbidities such as chronic kidney disease (CKD), diabetes, hypertension, metabolic syndrome and inflammation on all-cause mortality. Among the secondary objectives there is, again, assessment of SVD, which will complement the data derived from INDURE and RESILIENCE.

